During this meeting, the names of all 60 short-listed facilities were written on individual pieces of paper, folded and placed into six transparent plastic boxes - one for each sub-County. The total target sample of 48 facilities was divided between sub-Counties broadly in proportion to the number of facilities in the master list, but with rounding so that each sub-County had an even number of facilities in the trial. The Health Management Teams from each sub-County were invited in turn to select a piece of paper from their respective box, beginning with the Northernmost sub-County. The first facility selected was allocated to the intervention arm and the second to the control arm, the third to intervention and so on in succession. The name of each selected facility was written on a board, together with the allocation. For each selected facility, the records officer for the sub-county was asked to map the location and catchment area on a large map of the county. If a subsequently selected facility was found to have an overlapping catchment area with a facility previously selected, then the newly selected facility was rejected and another drawn from the box to take its place. This process continued until 48 facilities had been selected and allocated for the trial. This meeting generated a list of 24 intervention and 24 control facilities, with their location and catchment areas mapped to ensure that they do not overlap. In summary, the randomization is stratified by sub-County and ensures equal allocation to study arms within each stratum.

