### Sample size

We hope to analyse all the primary outcomes jointly and also to analyse most outcomes as ordinal variables (see Data management and analysis), thereby maximising power and aiding interpretation. However, for our sample size calculation, we consider power to detect an effect of the intervention on one primary outcome, which we also assume to be a binary indicator that all attendances are made, as this is simple and conservative in the power achieved. The expected prevalence of these indicators in the control arm ranges between 30 and 80%. Little specific information on the likely intra cluster correlation (ICC) for any of the outcomes is currently available - we consider it may lie between 0.005 (low) and 0.025 (moderate). Our planned sample size is 48 clusters (24 per arm) and an average cluster size of 150. At a low ICC, the design effect (DE) will be 1.745 and hence the effective sample size (ESS) will be 2063 participants per study arm. At a moderate ICC, the DE will be 4.725 and hence the ESS will be 762 per arm. Power to detect absolute differences is lowest when the prevalence is 50% and highest when the prevalence is either high (towards 100%) or low (towards 0%). Here we consider the prevalence in the control arm to range between 50% (‘worst-case scenario’) and 80% (‘best-case scenario’). We consider the standard 5% significance level. If the prevalence of the outcome is 50% in the control arm, the sample size provides 80% power to detect an improvement to 54.5% in the intervention arm if the ICC is low and 57.5% if the ICC is moderate. If the prevalence of the outcome is 80% in the control arm, the sample size provides 80% power to detect an improvement to 83.5% if the ICC is low and 85.5% if the ICC is moderate.

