#### Baseline data

In order to understand the baseline characteristics and behaviour of the sample population, a retrospective audit of ANC, delivery and PNC will be undertaken by chart review at selected facilities. The retrospective chart audit entails collection of data from all facilities, between January and December 2016 in the year preceding the commencement of participant enrolment. The data were collected according to a pre-determined proforma. This included data on primary trial outcomes, retention at the local facility and continuity of care. Data were anonymised at collection and each new entry was assigned a unique retrospective *Afya* identifier number.

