#### Final analysis

Final analyses will be by intention-to-treat, based on all enrolled mothers who were pregnant during the recruitment period (July 2017 to July 2018) and their children, regardless of whether they received the intervention or not. We will test for differences in the primary outcomes between the intervention and control arms using logistic regression for binary outcomes, and ordinal logistic regression for ordinal outcomes, adjusting for clustering using random effect models.

Provided there is no qualitative difference between the odds ratios for the effect of the intervention across the primary outcomes, then only the summary odds ratio will also be presented. This will be the primary effect measure for the trial. It will be estimated using independence estimating equations because not all participants will be eligible for all outcomes (e.g. vaccination of infants who died) and this approach avoids any implicit imputation of outcomes for ineligible participants.

Besides the issue of ineligible outcomes described previously, there should be no completely missing data on the primary outcomes. If a record of attendance cannot be found in the patient records in the study area, this will be interpreted as failure to attend. However, participants may make visits to facilities outside the study area, often in relation to temporarily or permanently moving to reside outside the study area. As described in Section Collecting data on visits to facilities outside the study area, data on visits outside the study area will be available for all higher-risk participants, and dependent on telephone interviews also available (though approximate) for up to half the lower-risk participants.

We plan to conduct our primary analysis based only on data on lower-risk participants from visits within the study area if it seems this will not lead to bias, but to use the approximate number of visits outside the study area from (up to) half the lower-risk participants to impute these additional visit data for the remaining participants if it seems bias will otherwise arise. We prefer not to impute visits out of the study area unless this is required because the data on visits outside the area by lower-risk participants are only approximate.

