The precise criteria by which will we judge if bias is likely, and exactly how imputation will be conducted if necessary, will be specified in our analysis plan. If imputation is conducted then the analysis based on imputed data will be considered primary.

In our primary analysis we will adjust for key predictors of the primary outcomes, and any other baseline factors of clusters or individual participants for which an important imbalance is seen between arms. We will also carry out sub-group analyses to examine whether the effect of the intervention differs by wealth/multi-dimensional poverty quintile to understand the equity impact of the intervention.

The final analysis will be presented according to the consolidated standards of reporting trials (CONSORT) requirements for cRCTs [45, 46]. Both the interim and final analyses will be conducted by the trial statisticians. A detailed statistical analysis plan will be prepared and finalized in consultation with the Trial Steering Committee (TSC)/DMC before analysis begins.

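### The adjustment rule names neither the sub-County strata nor the 2016 facility baseline, and its imbalance limb is a poor way to choose them: tests may be conservative and precision forgone

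*Protocol article*

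**What the plan says.** **Design.** Randomization describes drawing facilities within each of six sub-Counties and assigning them alternately to intervention and control: "In summary, the randomization is stratified by sub-County and ensures equal allocation to study arms within each stratum". Allocation took place in January 2017.

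**Baseline.** The Baseline data section describes a retrospective chart audit for January to December 2016. On its content: "This included data on primary trial outcomes, retention at the local facility and continuity of care". The stated purpose is to understand the population. On coverage, the section first says the audit "will be undertaken by chart review at selected facilities", and then that it takes in all facilities. It also moves from the future tense to the past.

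**Analysis.** Final analysis plans logistic or ordinal logistic regression for each outcome, "adjusting for clustering using random effect models". The trial's primary effect measure is a summary odds ratio from independence estimating equations. The adjustment rule has two limbs: unnamed main predictors of the primary outcomes, and "any other baseline factors of clusters or individual participants for which an important imbalance is seen between arms". The only covariate list is in Table 1, which the Fig. 1 legend cites for covariates. It includes level of facility but not sub-County or a 2016 outcome value. A detailed analysis plan is to follow.

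**The concern.** The second limb of the rule chooses covariates by what the data happen to show. That suits neither variable at issue here.

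- **Sub-County.** Each sub-County contributes equal numbers of facilities to the two arms, so an imbalance check has nothing to detect. The reason to include it is different. Stratified allocation removes between-sub-County variation from the treatment comparison. A model without stratum terms leaves that variation in the error, so the reported standard error exceeds the true one.
- **2016 facility value.** An imbalance check would pick it only if the arms differed by chance. The precision it brings does not depend on imbalance. It also has the merit of describing a period before allocation, whereas individual covariates are collected by facility staff after allocation.

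With 150 women per facility, the facility component is a large part of the error, so power and the width of the confidence interval are at stake. Bias and false positives are not.

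**Working it through.** **Inputs from Sample size.** "Our planned sample size is 48 clusters (24 per arm) and an average cluster size of 150"; ICC 0.005 (low) or 0.025 (moderate). The documents give neither the share of between-facility variance lying between sub-Counties (f) nor the facility-level correlation between the 2016 and trial values (r). Both are assumptions below.

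**Step 1: reproduce the plan.** DE = 1 + 149 × ICC; ESS = 24 × 150 / DE = 3600 / DE.
- ICC 0.005: DE = 1.745, ESS = 2,063. The article agrees: "the design effect (DE) will be 1.745 and hence the effective sample size (ESS) will be 2063 participants per study arm".
- ICC 0.025: DE = 4.725, ESS = 762, as stated.

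The same DE can be written (1 − ICC) + 150 × ICC. That is 0.995 + 0.75 at the low ICC and 0.975 + 3.75 at the moderate one. The facility component is therefore 0.75/1.745 = 43% and 3.75/4.725 = 79% of the error.

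**Step 2: omit the strata.** Ratio of reported to true SE = √{DE / [(1 − ICC) + 150 × ICC × (1 − f)]}. Approximate type I error = 2 × [1 − Φ(1.96 × ratio)].

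| ICC | f | Ratio | SE too large by | Type I error |
|---|---|---|---|---|
| either | 0 | 1 | 0% | 5% |
| 0.005 | 0.20 | √(1.745/1.595) = 1.046 | 5% | 4.0% |
| 0.005 | 0.30 | √(1.745/1.520) = 1.071 | 7% | 3.6% |
| 0.025 | 0.20 | √(4.725/3.975) = 1.090 | 9% | 3.3% |
| 0.025 | 0.30 | √(4.725/3.600) = 1.146 | 15% | 2.5% |

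Over f = 0.10 to 0.50 at ICC 0.025 the excess runs from √(4.725/4.350), 4%, to √(4.725/2.850), 29%.

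A cluster-level simulation (linear scale, six strata of eight facilities assumed, 4,000 replicates per scenario) agrees on direction and is slightly milder. At f = 0.25, type I error without strata was about 4.0-4.1% at ICC 0.005 and 3.3% at ICC 0.025. At f = 0.50 it was about 3.3-3.7% and 1.9-2.1%. With no stratum effect, leaving the strata out did no harm. With strata in the model, type I error was about 5% throughout.

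**Step 3: add the 2016 facility value.** DE = (1 − ICC) + 150 × ICC × (1 − r²); ESS = 3600 / DE.

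| r | DE, ICC 0.005 | ESS | DE, ICC 0.025 | ESS |
|---|---|---|---|---|
| 0 | 1.745 | 2,063 | 4.725 | 762 |
| 0.5 | 1.5575 | 2,311 | 3.7875 | 950 |
| 0.6 | 1.475 | 2,441 | 3.375 | 1,067 |
| 0.7 | 1.3775 | 2,613 | 2.8875 | 1,247 |

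At ICC 0.025 and a control rate of 50%, the difference detectable with 80% power (t on 46 df) falls from 7.3 points to 6.5, 6.2 and 5.7. The 7.3 is in line with the article's 57.5% at half-point rounding.

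In the simulation, with strata already in the model, a baseline correlated 0.5 with the facility effect cut the SE by a further 2-4% at ICC 0.005 and 8-9% at ICC 0.025. At 0.7 the cuts were 6-10% and 16-21%. An uninformative baseline raised the SE by about 1%. The gains in steps 2 and 3 should not simply be added, because the 2016 value may carry some of the sub-County differences.

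**Step 4: degrees of freedom.** 48 facilities − 2 (intercept, arm) = 46. Removing 5 for sub-County and 1 for the baseline leaves 40. The critical t moves from 2.01 to 2.02.

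**The case against.** The strongest reply is that the first limb of the rule is unconditional. If the 2016 value predicts the outcomes well, it is one of the main predictors. If sub-County matters, so is sub-County, and if it does not, leaving it out costs nothing. The full list can properly sit in the analysis plan, which is not at hand, and Table 1 lists data sources rather than a model. This stands in part. A reader might infer that the primary model excludes both variables; the documents show only that it does not name them. What survives is that the article states its rule outright, and the stated imbalance limb cannot do this job.

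A reader might also infer that the standard errors are invalid. They are not: they are conservative, and only if outcomes differ between sub-Counties.

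The arithmetic is for one binary outcome on a linear scale, whereas the primary measure is a pooled odds ratio from independence estimating equations. That is fair. The percentages do not transfer exactly. The direction does, since facility-clustered standard errors without stratum terms also retain the between-sub-County variation.

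The correlation may be lower than assumed. Thirty of the 48 facilities were not operating during the 2017 strike, and the audit recorded retention at the local facility whereas trial visits count anywhere in Siaya County. This also stands, and is why the baseline gain is given as a range that includes none.

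Finally, a reader might take the coverage wording in Baseline data as a contradiction. The article elsewhere uses selected for the trial facilities, so all of the selected facilities is an ordinary reading. It needs clarifying, no more.

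**Conclusion.** The point holds as a recommended improvement, not as an error that threatens validity. The stated rule leaves the randomisation strata and an already planned baseline of the primary outcomes unnamed, and relies partly on a criterion that cannot select the first and would select the second only by chance.

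The cost of omitting the strata ranges from nothing, if sub-Counties do not differ, to a standard error 9-15% too large at ICC 0.025 (5-7% at ICC 0.005) on an assumed 20-30% share. The cost of omitting the baseline is an effective sample size of 762 rather than 950-1,247 per arm at ICC 0.025, or 2,063 rather than 2,311-2,613 at ICC 0.005, on an assumed correlation of 0.5-0.7. A claim of large, free precision would go too far: both inputs are assumed, the gain is smaller at the low ICC, and a baseline that predicts nothing costs about 1% in standard error.

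**What to change.** In the analysis plan, before any comparison by arm:

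- Include sub-County as fixed effects unconditionally.
- If the audit covers all 48 facilities, include the facility's 2016 value of the outcome as a cluster-level covariate.
- Apply both in the outcome-specific random-effects models and in the summary odds ratio from independence estimating equations, with facility-clustered standard errors and t-based inference on about 40 df.
- Do not rely on observed imbalance to bring in either variable.
- In Baseline data, state whether the two descriptions of coverage both mean the 48 trial facilities, and whether collection is complete.

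The cost is wording, about six cluster degrees of freedom, and a treatment odds ratio that is conditional on these covariates and should be reported as such. No new data are needed if the audit is complete. If it is not, the sub-County terms can still be included.

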## Discussion

The ongoing intervention seeks to positively impact maternal and child healthcare-seeking in one of the poorest provinces in Kenya, improving survival and reducing morbidity among the most vulnerable. It aims to achieve this by enhancing the demand for continuity of care from the antenatal period through to the postnatal and early life period, thereby maximising the gains obtained from each stage in these processes. Being amongst the first rigorous evaluations of maternal health incentive payments in East Africa, it will generate results of great policy interest for the region and sub-Saharan Africa as a whole. In addition to providing evidence on the role of conditional cash transfers in encouraging uptake of maternal and child healthcare visits, it will also provide evidence on the benefit of an extended continuum of care on child survival and maternal health.

Both a strength and limitation of this trial design is the reliance on functioning technical systems to track health service use and make the cash transfers. In the rural Kenyan context, electricity provision may be unreliable and mobile phone coverage inconsistent. This may pose a risk to trial protocol adherence and manual back-up systems have been devised in the event of technical failure. A further limitation of the design is the follow up of a limited sub-sample of participants for the telephone interviews. While this is the most pragmatic and cost-effective design for the trial, a larger sample size would provide us with greater power to detect smaller effects.

It is further acknowledged, that this study addresses only the demand-side factors that negatively affect timely and repeated care-seeking in this context. Supply-side factors affecting care-seeking and health outcomes may reduce the observed effectiveness of the intervention. For example, it is well-documented that poor service quality and negative staff attitudes are also among the factors that keep women away from the health facilities [10]. The process evaluation previously described will assist in measuring the likely effect of supply-side factors on trial outcomes. Similarly, patient perceptions of quality of care will be collected during the telephone interviews. In addition, a sample of key informant interviews will be conducted with healthcare providers to explore provider perceptions of quality of care since the introduction of the scheme and their perception of whether the “carrying capacity” of their institution is being exceeded. It is likely however, that this will remain an area for future study.

## Trial status

The trial is ongoing. Recruitment began on 15 July 2017 and ended on 31 July 2018. Protocol Version 2.1, 26 December 2018.

## Abbreviations

ANC: Antenatal care
cCRT: Cluster randomized controlled trial
CCT: Conditional cash transfer
CHMT: County health management team
CHVs: Community health volunteers
CPI: Consumer price index
CRO: County records officer
DMC: Data management committee
EDD: Expected delivery date
HDI: Human development index
ICC: Intra cluster correlation
ICERs: Incremental cost-effectiveness ratios
IPTp: Intermittent preventive treatment of malaria in pregnant women
KEPH: Kenya Essential Package for Health
MNCH: Maternal, newborn and child health
MOH: Medical officer of health
NFC: Near field communication
NICE: National Institute for Health and Care Excellence
PFI: Personal financial incentives
PMTCT: Prevention of mother-to-child transmission
PNC: Postnatal care
RMNCH: Reproductive, maternal, newborn and child health
SSA: Sub-Saharan Africa
SWAP: Safe Water and AIDS Project
TB: Tuberculosis
TSC: Trial steering committee
WHO: World Health Organization
